### Mood disorder measurement

‘Depression and Anxiety’ is assessed prior to surgery, 7 days post surgery, 3 months post surgery, and 12 months post surgery using the HADS questionnaire. The HADS is a brief self-report Likert scale where participants report how well a depressive or anxious symptoms describes them in the past 7 days (e.g. ‘I felt tense or “wound up”’ [50]).

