The literature suggests a strong correlation between the two tasks of the psychomotor-attention composite, detection and identification, for simplicity’s sake assumed to be in the region of *r* = 0.8 is expected (for example, see the similarities present on scores from the research of Hammers et al., 2012; [55] and Lim et al., 2012 [56]). Further, the variances for pre and postsurgery will be standardised to 1. The variance of the composite is calculated as the sum of pre and postsurgical variances plus twice the correlation of the composite tasks; 2 + 2 (0.8) = 3.6. Therefore, to estimate the effect of MCI (and by extension, cognitive change after surgery), we divide the combined effect size for the psychomotor-attention composite by the standard deviation of the effect size, that is the square root of the variance of the composite. From Lim et al., the effect of MCI size of the change in reaction speed for the detection and identification tasks were −0.33 and −0.63, respectively, giving a total reduction in reaction speed effect size of −0.96. Therefore, the total effect of MCI (and by extension, cognitive change after surgery) upon the psychomotor-attention composite is equal to: −0.96/√3.6 = −0.51. Given that NAC is unlikely to improve cognition beyond baseline estimates, it is proposed that NAC may instead ameliorate the severity of cognitive dysfunction compared with placebo. Given the limited available data, we have attempted to estimate an approximate protective effect based on the use of NAC in analogous conditions, such as traumatic brain injury [63]. Additionally, it is unrealistic to assume complete prevention of cognitive dysfunction. Therefore, a relative reduction in severity of cognitive dysfunction of 50 % represents an appropriate compromise to calculate the power. Given the likelihood of significant correlation in pre and postsurgery cognition scores, and in the absence of any identifiable correlation size, it is prudent to include an estimation of correlation patterns in the medium range (*r* = 0.50). A protective effect of NAC of 50 % would then set the expected effect of postoperative cognitive change as modulated by NAC at = −0.255. Assuming an alpha level of 0.05, power of 80 %, and a pre and postsurgical score correlation of 0.5, a sample size of 370 participants will have 80 % power to detect a minimum absolute effect size of 0.255 using an analysis of covariance (ANCOVA) model. This sample size includes approximately equal representation across stratification by age and surgery type for intervention.

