### Secondary analyses

Linear mixed-model ANCOVA will be conducted to model the differences in cognitive changes between treatment groups by fitting a linear curve to represent the relationship between performance on tasks and time point. The magnitude of the differences between treatment groups will be expressed as Cohen’s *d*.

Between-group differences on the individual tasks of the neuropsychological battery will be examined. Similar to the primary analysis, an ANCOVA will be used to examine the performance of participants on each of the neuropsychological battery tasks. Included in the analyses will be the individual CBB tasks, detection, identification, one-card back, and one-card learning; RBANS tasks, the COWAT, and Trail Making Tests A and B. Data will be represented as a linear mixed-effects model, comparing the performance of the NAC group compared to the control group over time. The magnitude of difference between treatment groups will be calculated as Cohen’s *d*.

Between-group differences on measures of delirium and mood dysfunction will be analysed using a chi-square test using the CAM and HADS measures. Participants will be classified dichotomously as displaying symptoms of delirium or mood dysfunction according to established cut-off points; 11 points on either anxiety or depression for the HADS, or fulfilment of delirium criteria according to the CAM.

Between-group differences on measures of quality of life will be analysed using an ANCOVA to examine changes over the course of the trial, controlling for baseline values as a covariate. Between-group differences will be examined for change across time from baseline scores to 3 months and 12 months. A linear mixed-effects model will be used to represent the data comparing treatment groups, with the magnitude between treatment groups expressed as Cohen’s *d*.

Between-group differences in serum levels of biological markers will be examined prior to surgery and at POD2 in order to capture the surgical stress response. An ANCOVA will be performed to examine the between-group differences over time, with baseline values acting as a covariate. Data will be graphed using a linear mixed-effects model, with the magnitude of difference between treatments groups expressed as Cohen’s *d*.

A bivariate correlation analysis exploring serum biological marker levels and cognitive function will be calculated for each of the battery tasks.

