### Exploratory analyses

Subgroup analyses will be undertaken to examine the role of variables that may contribute to risk factors associated with POCD, such as demographic information, health and medical history, socioeconomic status, and other data collected during the study. These subgroup analyses can be examined using a multilevel modelling approach. For example, by treating the presence of POCD in a participant as an outcome level, it will be possible to examine the relative contributions of each independent variable to POCD (e.g. varying treatment effects for differing levels of demographics). This approach can also be expanded to further examine other participant outcomes, such as the presence of delirium, mood dysfunction, or a significant change in quality of life. For exploratory analyses focussed upon proportionate data, such as comparisons of dichotomous delirium or mood dysfunction outcomes, McNemars’ test can be used to examine within-groups differences across time points. The role of perioperative pain upon POCD may also be explored as a potential cognitive trajectory modulator.

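### HADS is listed as a comparison with raw baseline scores, but the only between-group test is an unadjusted chi-square on a cut-off

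*Protocol article*

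**What the plan says.** Under Outcome variables, the protocol article lists mood on the HADS as a secondary outcome at day 7, 3 months and 1 year, with each follow-up set against the raw score from before surgery. The WHOQOL-BREF item carries the same sentence. In that list, only delirium is described as recorded in two categories.

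Under Mood disorder measurement, mood "is assessed prior to surgery, 7 days post surgery, 3 months post surgery, and 12 months post surgery using the HADS questionnaire". Table 1 agrees: HADS has a presurgical assessment, whereas the CAM is not scheduled before surgery.

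Under Secondary analyses: "Between-group differences on measures of delirium and mood dysfunction will be analysed using a chi-square test using the CAM and HADS measures". The cut-offs are "11 points on either anxiety or depression for the HADS, or fulfilment of delirium criteria according to the CAM". No covariate is named. In the same section: "Between-group differences on measures of quality of life will be analysed using an ANCOVA to examine changes over the course of the trial", with the baseline value as covariate.

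Under Exploratory analyses, for dichotomous delirium or mood outcomes, "McNemars’ test can be used to examine within-groups differences across time points". Multilevel modelling of the presence of mood dysfunction is also mentioned as a possibility.

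**The concern.** A two-arm chi-square on a yes/no classification uses neither the raw score nor the baseline. The outcome list promises both. A patient already at 11 or more before surgery who stays there counts the same as a new case, and a change that does not cross the cut-off does not count at all.

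HADS has been grouped with the CAM, which is binary and has no presurgical measurement. By design it resembles WHOQOL-BREF, which is also a score with a baseline and which does get a baseline-adjusted ANCOVA. At stake are the precision of one secondary outcome at three visits and whether the reported result matches the outcome as listed.

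**Working it through.** **1. The plan's own figure.** The sample size section claims that "a sample size of 370 participants will have 80 % power to detect a minimum absolute effect size of 0.255". Its other inputs are ANCOVA, alpha 0.05 and r = 0.5 between the scores before and after surgery. With two-sided alpha (sidedness is not given):

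n per arm = 2(1 − r²)(z₀.₉₇₅ + z₀.₈₀)²/d² = 2 × 0.75 × (1.960 + 0.842)²/0.255² = 181.1, so 182 per arm and 364 in total. This is within 2% of 370, so the figure reproduces. It concerns the primary outcome; no power is claimed for HADS.

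**2. Assumptions for HADS.** The documents give no HADS distribution, prevalence above the cut-off, correlation or effect. I assume a normal score with a shift of 0.255 SD and r = 0.5 (both borrowed from the primary outcome), and 185 per arm with no losses.

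**3. Continuous analyses of one subscale.**
- Baseline-adjusted ANCOVA: SE = √0.75 × √(2/185) = 0.0900; power = Φ(0.255/0.0900 − 1.960) = 80.8%.
- Raw score without baseline: SE = √(2/185) = 0.1040; power = Φ(0.255/0.1040 − 1.960) = 68.9%.

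**4. Cut-off on a single score.** With control prevalence p, the treated prevalence is 1 − Φ(z₁₋ₚ + 0.255). For p = 0.10 that is 1 − Φ(1.282 + 0.255) = 0.0622, and the two-proportion test has 26.4% power. Efficiency relative to ANCOVA is φ(z)²/[p(1 − p)] × (1 − r²); for p = 0.10, 0.1755²/0.09 × 0.75 = 0.342 × 0.75 = 0.257.

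**5. The plan's actual rule, either subscale.** Two normal subscales with correlation 0.6 (assumed), both shifted by 0.255 SD. A patient is a case if either exceeds its cut-off.

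| Control prevalence per score | Treated prevalence | Chi-square power, single score | Efficiency v ANCOVA, single score | Either-rule prevalence, control / treated | Chi-square power, either rule |
|---|---|---|---|---|---|
| 0.05 | 0.0287 | 18.2% | 0.17 | 0.0845 / 0.0500 | 26.2% |
| 0.10 | 0.0622 | 26.4% | 0.26 | 0.1610 / 0.1037 | 36.9% |
| 0.15 | 0.0983 | 32.5% | 0.32 | 0.2328 / 0.1584 | 43.7% |
| 0.20 | 0.1364 | 37.2% | 0.37 | 0.3008 / 0.2136 | 48.3% |
| 0.30 | 0.2179 | 43.7% | 0.43 | 0.4273 / 0.3243 | 53.4% |
| 0.50 | 0.3994 | 49.4% | 0.48 | 0.6476 / 0.5419 | 54.5% |

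**6. Sensitivity.** Varying the subscale correlation from 0.4 to 0.8 moves the either-rule power to between 24% and 57%. With a weaker baseline correlation of r = 0.3, the single-score efficiency is 0.20 to 0.58. From dichotomising alone, with no baseline adjustment in either analysis, it is 0.22 to 0.64. In every case tried the chi-square has less power than even the unadjusted raw-score comparison (68.9%).

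**The case against.** The strongest reply is that the endpoint is named as mood disorder, which can fairly be read as a category, and that the Secondary analyses section classifies it by established cut-offs. On that reading only the raw-score sentence is out of place. This stands as far as it goes, but one of the two sections is then still wrong.

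A reader might infer that counting patients already above the cut-off before surgery biases the comparison. It does not: under 1:1 randomisation such patients are expected equally in both arms. They cost precision only.

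A reader might also say that the baseline is discarded altogether. That holds for the treatment comparison. The exploratory McNemar test can use it, but that test is optional and within-group, and the multilevel modelling is exploratory too. Neither compares the arms on baseline-adjusted scores.

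The size of the loss depends on assumptions. One could pick a single score at 10% prevalence and a 0.3 SD shift and report 34% against 91% power. That shift is not in the documents, and the plan counts a case on either subscale. Under that rule (subscale correlation 0.6) the same shift gives about 47% at 10% per subscale and 56–61% at 15–20%.

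Finally, mood appears in none of the aims or hypotheses, so little inferential weight rests on it. That limits the importance of the point but does not remove the contradiction.

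Leaving the matter to a statistical analysis plan is not an answer, because the article already fixes a test and a cut-off that conflict with its own outcome list.

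**Conclusion.** The point holds as an inconsistency with a cost in precision. The HADS outcome is defined by reference to raw baseline scores, and the only planned between-group analysis uses neither the raw scores nor the baseline. This follows from the text and needs no calculation.

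The size is conditional on a normal score and on the borrowed r = 0.5 and 0.255 SD: about 81% power for baseline-adjusted ANCOVA, against about 18–49% for a single-score cut-off at 5–50% prevalence and about 26–54% under the either-subscale rule. Real HADS scores may be skewed, which these figures ignore.

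The documents do not support calling the chi-square invalid or biased, or a null HADS result close to uninformative. That most of the information is lost is likewise not a fixed result: with r = 0.3 it fails at a single-score prevalence of about 30% or more. The primary analysis is untouched.

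**What to change.** Reconcile the Outcome variables and Secondary analyses sections before unblinding, so that the choice cannot depend on the data. Analyse HADS-anxiety and HADS-depression as two continuous scores, each with its own baseline as covariate, by ANCOVA or the linear mixed model, as already planned for WHOQOL-BREF. Check the residuals for skew, as the primary analysis already provides, and consider transformation if needed. Keep the 11-point classification as a supportive analysis, preferably adjusted for the baseline score, for example by logistic regression. If the investigators do intend a categorical outcome, the raw-score sentence in the outcome list must change instead. That resolves the contradiction but gives up the precision.

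The cost is wording only: HADS is already scheduled at baseline and at all three follow-up visits. Two subscales mean two results per visit in place of one, which the report should make plain.

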#### Secondary

That administration of NAC in the perioperative setting is superior to placebo for reducing the severity of enduring cognitive change in the late postoperative period, as measured by changes in performance on the psychomotor-attention composite of the CBB 3 months post surgery, and 1 year post surgeryThat administration of NAC in the perioperative setting is superior to placebo for reducing the severity of cognitive change in the early postoperative period, as measured by changes on the Repeatable Battery for the Assessment of Neuropsychological Status (RBANS), the Controlled Oral Word Association Test (COWAT), and Trail Making Tests A and B (TMT) 7 days post surgeryThat administration of NAC in the perioperative setting is superior to placebo for reducing the severity of cognitive change in the late postoperative period, as measured by changes on the RBANS, COWAT, and TMT at 3 months post surgery, and 1 year post surgeryThat administration of NAC in the perioperative setting is superior to placebo for reducing serum levels of biomarkers of inflammation and oxidative stress in the postoperative phaseThat there is an inverse correlation between performance on the neuropsychological battery and serum biomarkers of oxidative stress, at baseline, in the postoperative period and at follow-up

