## Methods and design

A single-centre, randomised, double-blind, placebo-controlled clinical trial. A total of 370 participants are randomised into either a placebo or treatment (NAC) group in a 1:1 ratio.

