### Trial procedures

Participants undergo an initial recruitment and screening interview, a baseline assessment of cognition, mood, and quality of life prior to surgery, and follow-up visits at postsurgery day 2, day 7, 3 months, and 12 months. Serum sampling for biomarker assessment occurs immediately prior to surgery, and then again on postsurgery day 2 to correlate with peak oxidative stress levels (Fig. 1, Table 1). The SPIRIT checklist is provided as an Additional file 1.

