Stratification by age enhances parity between groups in terms of its effects upon cognition, in accordance with established risk factors [5, 37]. Despite the relative safety and success of orthopaedic operations compared with nonorthopaedic operations, the risk of cognitive dysfunction is still significant [3]. Accordingly, orthopaedic patients represent an opportunity to examine potential cognitive change that is less likely attributable to other factors. Additionally, stratification by orthopaedic and nonorthopaedic counteracts the wide variability of reported POCD in the literature [38]. Meta-analyses suggest small cognitive improvements from pooled data yet individual studies note an incidence of POCD as high as 45 % [38]. It is widely held that this variability is due mostly to discrepancies in diagnostic criteria [39] but the concern remains that a significant subset of individuals within the orthopaedic cohort do experience cognitive improvement. The literature to date has not provided the means to identify them prospectively, but it has been suggested that a low cognitive baseline secondary to chronic inflammation, pain, opioid consumption, and restricted mobility, coupled with the potential for surgical remedy, is a potent confounder of postsurgical cognition [40]. This complex and not yet fully characterised surgical profile suggests that the broad classification of surgeries into orthopaedic and nonorthopaedic may help to minimise any confounding in the collected data, with negligible loss of power with respect to a nonstratified design.

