### Blood levels of inflammation and oxidative stress

Serum samples are collected during placement of an intravenous line during surgery (baseline), and again in conjunction with routine postoperative bloods on postsurgery day 2. This is timed to capture the approximate time of peak postoperative inflammatory markers of approximately 24–72 h post surgery [52]. Blood samples (30 ml) are taken by research staff and spun in equal portions into separate plasma, serum, and whole blood aliquots. These are then stored onsite at −80 °C in preparation for analysis by research staff at the end of data collection.

Whilst surgery and anaesthesia are associated with a systemic inflammatory response, patients who develop POCD tend to show higher levels of inflammatory markers, including interleukin-(IL)1β [52, 53], relative to those with intact cognition. Similarly, markers of oxidative stress, previously correlated to neuroinflammation, may be upregulated in POCD [52]. Circulating inflammatory factors are thought to potentiate neuroinflammation through stimulation of microglia, which produce both pro-inflammatory cytokines and potent reactive oxygen species and are instrumental in neuronal dysfunction [45]. Thus, measurement of peripheral inflammation and oxidative damage are reflective of not only systemic inflammation in the postoperative context but also central neuroinflammatory processes. We intend to examine a panel of related biological correlates, focusing on inflammatory cytokines, the primary CNS antioxidant species and markers of oxidative damage to lipid, DNA, and protein. Unspecified consent has been requested to allow for the exploration of relevant biological markers should they be identified during the course of the trial. Changes in peripheral markers will be correlated to clinical improvements.

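### The biomarker aim concerns changes, but the named analysis correlates marker levels with cognitive function without adjustment; this fits one hypothesis and not the aim

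*Protocol article*

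**What the plan says.** Four places in the protocol article bear on this.

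- **Aims, Secondary:** one aim is to examine how changes in cognition and biomarkers correlate.
- **Blood levels of inflammation and oxidative stress:** "Changes in peripheral markers will be correlated to clinical improvements".
- **Hypotheses, Secondary:** the last hypothesis posits an "inverse correlation between performance on the neuropsychological battery and serum biomarkers of oxidative stress, at baseline, in the postoperative period and at follow-up". This is about levels at each period, not changes.
- **Secondary analyses:** "A bivariate correlation analysis exploring serum biological marker levels and cognitive function will be calculated for each of the battery tasks". No change score, time point, covariate or treatment arm is mentioned.

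On sampling, Trial procedures states: "Serum sampling for biomarker assessment occurs immediately prior to surgery, and then again on postsurgery day 2". On age, the randomisation section says: "Stratification by age enhances parity between groups in terms of its effects upon cognition, in accordance with established risk factors". The hypotheses expect NAC to improve cognition and to lower postoperative markers.

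**The concern.** The analysis section names a method, and that method does not match the aim. A correlation of levels reflects stable differences between people as well as any shared response to surgery. Older patients may be slower and have higher markers before and after the operation, whether or not the two are directly linked. NAC, if it works as hypothesised, moves both variables and adds a further component to a postoperative correlation taken over both arms. The other continuous secondary outcomes in the same section (battery tasks, quality of life, markers between groups) are analysed with baseline as a covariate. This analysis is the exception.

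At stake is how a significant result is read. The protocol's rationale is that oxidative stress and inflammation contribute to cognitive decline. A correlation produced by age could be taken as support for that mechanism.

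**Working it through.** **The plan's own figure.** The protocol gives no figure for the correlation, only for the primary ANCOVA: "Assuming an alpha level of 0.05, power of 80 %, and a pre and postsurgical score correlation of 0.5", and "a sample size of 370 participants will have 80 % power to detect a minimum absolute effect size of 0.255". Taking alpha as two-sided, n per arm = 2(1.96 + 0.842)² × (1 − 0.5²)/0.255² = 2 × 7.849 × 0.75/0.0650 = 181.1, so 182 per arm or 364 in total. With 185 per arm the power is 80.8%. The 370 is reproduced closely, so N = 370, 1:1 allocation, a 0.255 SD effect on cognition and a pre-post correlation of 0.5 are used below.

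**Assumptions not in the protocol.** NAC lowers the marker by 0.5 SD (varied below). Age correlates equally with marker and cognition, at 0.1, 0.2 or 0.3, and does so to the same extent before and after surgery. The marker pre-post correlation is also 0.5. There is no direct marker-cognition link. The arms are analysed together.

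**Formulas.** With effects dc on cognition and db on the marker, and age correlations a and b, the correlation of postoperative levels is

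r = (a·b + dc·db/4) / √[(1 + dc²/4)(1 + db²/4)].

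The chance of p < 0.05 follows from Fisher's z: atanh(r) × √367 compared with 1.96. The smallest nominally significant |r| at N = 370 is 0.102.

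**Treatment alone.** r = (0.255 × 0.5/4)/√(1.0163 × 1.0625) = 0.0319/1.0391 = 0.031, giving 9%. Other marker effects:

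| Marker effect (SD) | r | Chance of p < 0.05 |
|---|---|---|
| 0.2 | 0.013 | 6% |
| 0.5 | 0.031 | 9% |
| 0.8 | 0.047 | 15% |
| 1.0 | 0.057 | 19% |

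**Age and treatment together**, marker effect 0.5 SD:

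- age 0.1 with both: (0.010 + 0.0319)/1.0391 = 0.040, giving 12%
- age 0.2 with both: (0.040 + 0.0319)/1.0391 = 0.069, giving 26%
- age 0.3 with both: (0.090 + 0.0319)/1.0391 = 0.117, giving 62%

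Simulations of trials of 370 gave 25% to 28% for age 0.2 and 57% to 62% for age 0.3. The spread reflects simulation error and details of the set-up.

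**Baseline levels.** Treatment cannot act here, so r = a·b. This gives 0.04 (12%) for age 0.2 and 0.09 (41%) for age 0.3.

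**Change against change.** With a pre-post correlation of 0.5, a change score has variance 2(1 − 0.5) = 1, and an age effect that is stable over time cancels. Only the treatment term is left: r = 0.031, or 9%, for every age correlation. Simulation gave 9% to 10%.

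**Regression adjusted for arm, age and both baselines.** Simulation gave about 5% in every scenario, which is the nominal rate.

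Moving from levels to changes therefore removes the stable age component, and adjusting for arm removes the rest.

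**The case against.** The strongest reply is that the levels analysis answers a hypothesis the protocol does state. The last secondary hypothesis concerns performance and markers at each period, baseline included, and a bivariate correlation addresses that directly. It posits only an association. If older patients are slower and have higher markers, that association exists, and the percentages above count as false positives only for a question about a direct link. The analysis is described as exploring, and nothing says that a significant result will be taken as proof of mechanism. This stands. It is why the levels correlation should be kept, and why the harm lies in interpretation. It does not cure the mismatch with the aim, which needs change in cognition on any reading.

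A reader might infer three stronger things that the document does not support.

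- **That the plan pools raw values over both arms.** The text is silent on arms and on raw values. Pooling is the natural reading of one correlation per task, but it is not written.
- **That no correlation of changes is planned.** The biomarker section does announce one. The fault is that the analysis section does not carry it through.
- **That treatment is a main source of the artefact.** At the protocol's effect on cognition, treatment alone gives r of at most 0.057 for marker effects up to 1.0 SD, below the critical 0.102, and it cannot affect the baseline correlation. The larger figures come mainly from age.

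It can also be said that correlating changes, as the biomarker section announces, is repair enough. It removes most of the problem if the age effect is stable over time. It leaves the treatment component, and would leave more if older patients also change more on both measures.

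**Conclusion.** The point holds as a mismatch between aim and method. The aim and the biomarker section speak of changes, while the last hypothesis and the analysis section speak of levels. The named analysis is unadjusted by definition, so it cannot separate a shared response to surgery from stable differences between patients.

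The size is illustrative. With no direct link, the chance of nominal significance for postoperative levels is about 9% from treatment alone, about 25% with age correlations of 0.2, and about 57% to 62% with 0.3. It is about 9% for changes and about 5% after adjustment. Only N, the allocation ratio, the 0.255 SD effect and the cognitive pre-post correlation come from the protocol. The age correlations, the marker effect, the marker pre-post correlation and pooling are assumptions, and at age correlations of 0.1 the figure is only about 12%.

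This is a secondary, exploratory analysis. The primary comparison and the baseline-adjusted comparison of markers between arms are untouched. It is worth correcting, but it does not threaten the trial's main conclusion.

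**What to change.** In Secondary analyses, for the aim about changes, specify a linear regression of each follow-up task score on the day 2 marker, adjusted for the baseline marker, the baseline score on that task, treatment arm, age and surgery stratum. Report the partial correlation with its 95% confidence interval.

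Keep the bivariate correlation of levels, including the one at baseline, as a descriptive analysis for the last secondary hypothesis. Replacing it outright would leave that hypothesis without an analysis. State whether it is computed within arms or over both.

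Then align the wording of the aim, the hypothesis, the biomarker section and the analysis section. In doing so, say what the hypothesis means by biomarkers at follow-up, since blood is taken only before surgery and on day 2. The available pairing is the day 2 marker with later cognitive scores.

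The cost is revised wording and a little more analysis work. All the variables are already collected, and the stored samples are to be analysed only once data collection ends.
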